Uncertainty remains regarding the clinical relevance of exercise training across the entire range of ILDs. Patients with IPF appear to have smaller gains in functional capacity than those with ILD of other aetiology [24]. This raises the possibility that some forms of ILD may respond to exercise training better than others. Common manifestations of ILD, such as exercise induced hypoxia and pulmonary hypertension [2,9], may also affect the improvements that may be achieved. Hypoxaemia impairs maximal exercise performance [3] and pulmonary hypertension in ILD is associated with considerably reduced exercise capacity and greater exercise limitation [25-27]. In an uncontrolled study evaluating the relationship between response to exercise and disease aetiology and severity in forty-four subjects with ILD of varying aetiology, less severe lung function, less oxyhaemoglobin desaturation and less pulmonary hypertension were associated with greater improvement in functional capacity in patients with IPF [28]. This relationship persisted at six months, suggesting that those with less advanced IPF may be able to achieve sustained benefits from exercise training. This relationship was not seen in subjects with other ILDs. It is therefore possible that the timing of exercise training may be important for patients with IPF, whereas patients with other forms of ILD may benefit regardless of disease severity.

In order for exercise training to be widely adopted in clinical practice, clinicians require more information regarding its role across the disease spectrum. The aims of this study are 1) to establish the impact of exercise training on ILDs of different aetiology and severity and 2) to identify whether there is an optimal timing for exercise training to achieve maximal benefit. We hypothesise that exercise training will be effective regardless of disease severity in patients with non-IPF related ILD, whereas in patients with IPF, the response to exercise training will be greatest in those with less severe disease.

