### Sample size

One hundred and sixteen participants will be required to detect a significant difference in the primary outcome measure of change in functional exercise capacity (6-minute walk distance [6MWD]). This is based on the 80% probability of detecting a difference in the change in 6MWD between the intervention and control group using data from our previous randomised control trial [17] and Cochrane review [24]. Our sample size calculation of 116 has been powered to include the required number of participants in the three most commonly observed ILD subgroups: IPF, dust-related ILD and connective tissue disease-related ILD. To detect a true difference in the change in 6MWD in subjects with IPF, a total of 72 subjects, 36 in each group, is required. This is based on the lower limit of the range for the minimal important difference (MID) of 29m [30] with a standard deviation (SD) of 43m. To detect a true difference in the change in 6MWD between groups using the upper limit of the MID of 34m [30] with SD 43m, a total of 54 subjects, 27 in each group, would be required. In subjects with dust-related ILD, a total of 22 subjects, 11 in each group, is required. This assumes that the true difference between groups is 52m with SD of 40m. In subjects with connective tissue disease-related ILD, 22 subjects, 11 in each group, is required, assuming a difference of 38m with SD 30m.

Data from our previous study [28] indicate that to detect a relationship between carbon monoxide transfer factor (TLCO) and change in 6MWD following pulmonary rehabilitation with 80% power will require 31 subjects in the pulmonary rehabilitation group. This assumes that the true change in 6MWD is 15 meters for each 10% change in baseline percent predicted TLCO. To detect a relationship between degree of pulmonary hypertension and change in 6MWD with 80% power will require 35 subjects in the pulmonary rehabilitation group. This assumes that the true change in 6MWD is 17 meters for each 10mmHg change in baseline right ventricular systolic pressure.

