#### Statistical analysis

Data will be analysed using intention-to-treat principles, with inclusion of all available data regardless of whether the intervention is completed. The response of exercise training and control groups will be compared for change in exercise and HRQoL variables using linear mixed model analyses. Planned subgroup analyses will be conducted for participants with IPF, dust-related ILD and connective tissue-related ILD. Multiple regression analysis will be undertaken to establish which subjects respond best to exercise training and when this treatment should be offered, with change in 6MWD following exercise training as the dependent variable. Baseline demographic and physiological variables such as age; gender; disease aetiology; percent predicted TLC; percent predicted FVC; TLCO; pulmonary artery pressure; and the extent of oxyhaemoglobin desaturation during exercise will be used as predictors.

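### Effect by aetiology is an aim, but no planned analysis tests whether the training-versus-control effect differs between IPF, dust-related and connective tissue disease-related ILD

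*Protocol article*

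**What the plan says.** The first aim, in the Background of the protocol article, is "to establish the impact of exercise training on ILDs of different aetiology and severity". The closing paragraph of the Discussion repeats aetiology as part of what the study was designed to define.

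Three parts of the plan bear on this aim:

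- **Main comparison** (Statistical analysis): "The response of exercise training and control groups will be compared for change in exercise and HRQoL variables using linear mixed model analyses". No term for group by aetiology is mentioned.
- **Subgroups** (Statistical analysis): "Planned subgroup analyses will be conducted for participants with IPF, dust-related ILD and connective tissue-related ILD". The Sample size section gives each subgroup its own calculation, with its own effect and SD. For dust-related ILD, for example, "This assumes that the true difference between groups is 52m with SD of 40m". The total of 116 is the sum of the three. No power is given for a difference between subgroups.
- **Regression** (Statistical analysis): a multiple regression is meant to show who responds best and when training should be offered, "with change in 6MWD following exercise training as the dependent variable". The predictors are "Baseline demographic and physiological variables such as age; gender; disease aetiology; percent predicted TLC; percent predicted FVC; TLCO", followed by pulmonary artery pressure and exercise desaturation. Randomised group is not listed. The Sample size section sizes the two relationships it considers on trained participants. For transfer factor, detecting the relationship "with 80% power will require 31 subjects in the pulmonary rehabilitation group".

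**The concern.** Whether response to training depends on aetiology is a question about a difference between treatment effects. A subgroup test asks something else: whether the effect in that subgroup differs from zero. Its answer depends on the subgroup's size and SD as well as on the effect. Here there are 36, 11 and 11 participants per arm, with SDs of 43, 40 and 30 m. A significant result in IPF beside a non-significant one in dust-related ILD would say little about whether the two differ.

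The regression does compare aetiologies. As described, however, it compares change after training and does not use the control arm. The Background says that prognosis differs markedly between IPF, dust-related and connective tissue disease-related ILD. A difference in change among trained patients could therefore reflect a different course of disease and not a different response.

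What is at stake is who gets offered training. A chance pattern of p-values, or a difference in natural course, could be read as benefit confined to certain aetiologies.

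**Working it through.** **Inputs** (Sample size section): 80% power ("This is based on the 80% probability of detecting a difference in the change in 6MWD between the intervention and control group"). IPF: 36 per arm, 29 m, SD 43 m (27 per arm at 34 m). Dust-related: 11 per arm, 52 m, SD 40 m. Connective tissue disease-related (CTD): 11 per arm, 38 m, SD 30 m. Alpha is not stated; two-sided 5% is assumed. No dropout is assumed.

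**1. Reproducing the plan.** A two-sample t-test (noncentral t) with these inputs needs 36, 27, 11 and 11 per arm for IPF at 29 m, IPF at 34 m, dust and CTD. This matches the plan exactly, and 72 + 22 + 22 = 116. A one-sided 5% alpha gives 28, 20, 8 and 8, which does not match. So each subgroup was sized for its own test, with power of about 81%, 83% and 81%.

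**2. Standard errors.** SE = SD × √(2/n per arm):
- IPF: 43 × √(2/36) = 10.1 m
- Dust: 40 × √(2/11) = 17.1 m
- CTD: 30 × √(2/11) = 12.8 m

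The 95% CI half-widths (t with 70, 20 and 20 df) are about 20, 36 and 27 m.

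**3. Same true effect in all three subgroups.** With independent subgroups and powers p1, p2, p3, the chance that some tests are significant and others not is 1 − p1·p2·p3 − (1−p1)(1−p2)(1−p3).

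| Common effect | Power IPF / dust / CTD | All significant | None significant | Mixed |
|---|---|---|---|---|
| 29 m | 0.806 / 0.367 / 0.578 | 0.171 | 0.052 | 0.777 |
| 34 m | 0.911 / 0.475 / 0.715 | 0.310 | 0.013 | 0.677 |
| 38 m | 0.959 / 0.564 / 0.807 | 0.436 | 0.003 | 0.561 |
| 40 m | 0.973 / 0.607 / 0.845 | 0.499 | 0.002 | 0.499 |
| 52 m | 0.999 / 0.826 / 0.971 | 0.802 | 0.000 | 0.198 |

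Mixed results exceed 50% for common effects from 15 m to 39.5 m. IPF significant with at least one of the others not has probability p1(1 − p2·p3). At 29 m this is 0.806 × (1 − 0.367 × 0.578) = 0.63, and at 34 m it is 0.60.

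**4. Sensitivity.** With a common SD of 43 m, mixed results occur in 83% (29 m) and 81% (34 m) of trials. With a common SD of 30 m the figures are 67% and 49%. Three subgroups with exactly 80% power each would still give 1 − 0.8³ − 0.2³ = 48%.

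**5. Power of the test that answers the question.** Take the plan's own effects (29, 52, 38 m) and weights 1/SE². The weighted mean is 36.0 m. The noncentrality is Σ(effect − 36.0)²/SE² = 0.47 + 0.89 + 0.03 ≈ 1.38. A 2-df chi-square test at 5% then has about 17% power. For IPF versus dust alone, the difference is 52 − 29 = 23 m with SE √(10.1² + 17.1²) = 19.8 m. The ratio is 1.16 and the power about 21%. The difference detectable with 80% power is about 56 m for IPF versus dust and 46 m for IPF versus CTD.

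**The case against.** The strongest reply is that the article never says significance in one subgroup will be set against non-significance in another. It announces subgroup analyses, which could be estimates with confidence intervals from a single model. The aim can be read as estimating the effect within each aetiology, and stratified randomisation and separate sizing fit that reading. The idea that some forms respond better than others appears in the Background only as a possibility, and the stated hypothesis concerns severity within IPF and non-IPF disease. A full analysis plan, not shown, may contain an interaction term.

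Much of this stands. A reader might infer that the trial has committed itself to comparing p-values across subgroups; the text does not support that. Nor does it support saying that subgroups will usually appear to differ whatever the effect: that holds for common effects of roughly 15 to 40 m, and the plan itself assumes unequal effects. It would also be wrong to attribute the disagreement to sample size alone. The SDs differ too, and three separate tests often disagree even at equal power (48% at 80% each).

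What does not stand is that nothing is fixed. The article fixes separate sizing of the subgroups and the outcome of the regression assigned to finding who responds best. Taken together, these leave no stated randomised comparison between aetiologies. That the regression covers trained patients only is an inference from its outcome, its listed predictors and its sizing; the article does not say so outright.

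It may also be said that an interaction test with 17% power is of little use. That limits what the trial can show about differences. It does not make subgroup p-values a better basis for claiming one.

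**Conclusion.** The concern holds in this form: as described, neither the subgroup analyses nor the regression tests whether the training-versus-control effect differs by aetiology, although effect by aetiology is an aim. If results were read by significance across subgroups, a common true effect at either MID limit the plan cites would give a mixed picture in most trials: 78% at 29 m and 68% at 34 m, against 5% false positives for a valid interaction test. These figures rest on a two-sided 5% alpha, the planned sizes and SDs, independent subgroups and no dropout. At 34 m with an SD of 30 m throughout, the figure would be 49%. How far natural course would distort the regression cannot be calculated, because the article gives no control-arm change by aetiology.

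The matter should be corrected, but it leaves the overall training-versus-control comparison untouched.

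**What to change.** In the Statistical analysis section, specify one model in all participants with group, aetiology and group-by-aetiology terms, allowing the residual variance to differ by aetiology because the planned SDs do. Take the three subgroup effects and their 95% confidence intervals from that model. Base any statement that response differs by aetiology on the interaction, and not on subgroup p-values or the regression of change in trained patients.

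In the Sample size section, state that power for the interaction is low: about 17% for the planned effects, and about 21% for IPF versus dust-related ILD. Add that a non-significant subgroup is not evidence of no benefit, and a non-significant interaction is not evidence of no difference.

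The change is to wording and analysis only. Randomisation is already stratified by aetiology, and no further participants or data are needed. The price is an open concession that the trial has little power to show differences between aetiologies, which sits uneasily with the certainty promised in the Discussion.

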**Discussion:**

This trial will provide certainty regarding the role of exercise training in interstitial lung disease and will identify at what time point within the disease process this treatment is most effective. The results from this study will inform and optimise the clinical management of people with interstitial lung disease.

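### The regression meant to show how severity and timing affect response to training is in effect confined to the exercise arm, so it cannot tell response from prognosis

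*Protocol article*

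**What the plan says.** Under Statistical analysis, the article gives a regression the task of finding the best responders and the right time to treat: "Multiple regression analysis will be undertaken to establish which subjects respond best to exercise training and when this treatment should be offered". The outcome of that regression is fixed in the same sentence, which describes it as a model "with change in 6MWD following exercise training as the dependent variable". The predictors are listed as "Baseline demographic and physiological variables such as age; gender; disease aetiology; percent predicted TLC; percent predicted FVC; TLCO; pulmonary artery pressure", followed by exercise desaturation. Neither randomised group nor any group-by-covariate term is named.

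Under Sample size, the severity relationships are sized in one arm:

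- For TLCO, detection "with 80% power will require 31 subjects in the pulmonary rehabilitation group", on the assumption that "the true change in 6MWD is 15 meters for each 10% change in baseline percent predicted TLCO".
- For pulmonary hypertension, detection "with 80% power will require 35 subjects in the pulmonary rehabilitation group", on the assumption that "the true change in 6MWD is 17 meters for each 10mmHg change in baseline right ventricular systolic pressure".

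These figures are attributed to the team's previous study. The Background cites the same reference for a study of 44 subjects that it calls uncontrolled.

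The questions to be answered are in the Background. Aim 2 asks whether there is an optimal time to train. The hypothesis is that response depends on severity in IPF but not in other ILD. The abstract's Discussion says that the trial "will identify at what time point within the disease process this treatment is most effective".

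**The concern.** Asking at what severity training works best is asking about effect modification: does the difference between training and usual care change with TLCO or pulmonary pressure? Only a comparison of the severity slope between the two arms can answer that.

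Within the exercise arm, nine-week change is the training effect plus whatever would have happened anyway: disease course, residual test learning and regression to the mean. Any of these may vary with severity. The Background itself describes marked heterogeneity in clinical course. A marker that shifts change by the same amount in both arms modifies nothing, yet the exercise-arm regression would show it as a predictor of response. Advice on when to offer training could then rest on prognosis alone, although randomised controls are measured at the same visits.

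**Working it through.** **Assumptions not in the article.** Two-sided 0.05 (no alpha is stated), one marker at a time, equal marker spread and residual SD in both arms, no dropout.

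**1. The plan's total.** A two-sample t-test at 80% power gives:

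- IPF (29 m, SD 43 m): 36 per arm
- dust-related ILD (52 m, SD 40 m): 11 per arm
- connective tissue disease-related ILD (38 m, SD 30 m): 11 per arm

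These match the article: 72 + 22 + 22 = 116, or 58 per arm.

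**2. What 31 and 35 imply.** These cannot be reproduced directly, because the SD of TLCO, the SD of right ventricular systolic pressure (RVSP) and the residual SD are not given. Define k = slope × SD(marker) / residual SD. The slope test in n subjects has noncentrality k√n on n − 2 df. Solving for 80% power:

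- TLCO, n = 31: k = 0.521, so r = k/√(1 + k²) = 0.46
- RVSP, n = 35: k = 0.488, so r = 0.44

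For TLCO, an SD of 10, 15 or 20 points would imply a residual SD of about 29, 43 or 58 m (1.5 × SD / 0.521). The power results below depend only on k.

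**3. False attribution.** Suppose TLCO predicts change by s metres per 10% equally in both arms, so there is no effect modification. The exercise-arm test then has noncentrality 0.521 × (s/15) × √n.

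| Assumed s (m per 10% TLCO) | n = 31 | n = 58 |
|---|---|---|
| 2 | – | 8% |
| 5 | 15% | 25% |
| 10 | 46% | 74% |

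Each of these would be read as response to training. In a simulation with a common slope in both arms, the group-by-marker test was significant in about 5% of trials, its nominal rate.

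**4. Power of the test that answers the question.** A difference between two independent slopes has √2 times the standard error of one slope. The noncentrality is therefore k√(n/2) for n per arm, on 2n − 4 df. With the plan's slope in the exercise arm and zero in controls:

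| | TLCO | RVSP |
|---|---|---|
| 58 per arm | 0.521 × √29 = 2.80, 79% | 0.488 × √29 = 2.63, 74% |
| IPF only, 36 per arm | 0.521 × √18 = 2.21, 59% | 0.488 × √18 = 2.07, 53% |
| n per arm for 80% | 59 (118 in all) | 67 (134 in all) |

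If controls show 25% or 50% of the slope, power at 58 per arm falls to about 55% or 28% (TLCO) and 50% or 26% (RVSP).

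**5. Why one pooled interaction is not enough.** The stated hypothesis places the severity slope in IPF only, which is 36 of 58 per arm. If the marker has the same mean and spread in IPF and non-IPF, the pooled slope difference shrinks by 36/58 = 0.62. Noncentrality becomes 0.521 × 0.62 × √29 = 1.74 for TLCO and 1.63 for RVSP, giving about 41% and 37% power. A formal test that the interaction differs between IPF (36 per arm) and non-IPF (22 per arm) has noncentrality k/√(2/36 + 2/22) = 1.36 and 1.27 on 108 df. That is about 27% and 24% power, so the estimates with their intervals will carry more than this test.

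**The case against.** **The restriction to one arm is an inference.** The article never says that the regression uses the exercise arm only, and the abstract says more generally that effects of severity on outcomes will be evaluated. A full analysis plan, not shown, might include interactions. This stands as a caution. But the dependent variable, the baseline-only predictors and the sizing by the rehabilitation group all point the same way. Controls are offered training only after the six-month follow-up, so until then they have no change after training to analyse. The article commits to a specific analysis; this is not a detail merely left out.

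**A reader might infer that the trial's main result is non-randomised.** The documents do not support that. The primary outcome is compared between randomised groups by a linear mixed model. Aetiology is addressed by planned subgroup comparisons that are stratified at randomisation and separately sized. Only severity and timing are affected.

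**A reader might take 74% as the expected false-positive rate.** It is not. The slope behind it is hypothetical and is two-thirds of the plan's whole assumed slope. Nothing in the article shows that TLCO or RVSP predicts nine-week change without training. Clinical stability at entry, the best of two walk tests and the short interval all reduce the nuisance components. They do not remove them or make them independent of severity.

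**A reader might call the 80% power statement false.** It is labelled as a relationship with change following rehabilitation, so as a within-arm statement it is not contradicted. For TLCO across all ILD, the interaction test at 116 comes close (79%). The gap is in IPF, where the hypothesis sits.

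**Conclusion.** Wrong as written, for the severity and timing question only: aim 2 and the IPF severity hypothesis. Followed as stated, the regression cannot separate a marker of treatment response from a marker of prognosis.

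The size of the error is not knowable from the article. It ranges from slight (about 8% against a nominal 5% for a common slope of 2 m per 10% TLCO with 58 in the arm) to severe (about 74% for 10 m). The 80% power quoted for severity describes a within-arm association. For the question actually asked it is at best 79% (TLCO) and 74% (RVSP) across all ILD, and 59% and 53% within IPF. Those figures rest on a zero slope in controls and the other assumptions listed in the working.

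**What to change.** **Statistical analysis.** Fit all randomised participants: nine-week 6MWD on group, continuous baseline severity marker, group × marker, baseline 6MWD and aetiology. Let the group × marker effect differ between IPF and non-IPF through a group × marker × IPF term with its lower-order terms, and report group × marker within each. This tests the Background hypothesis directly. Base statements on who benefits, or when to offer training, on these interaction estimates with confidence intervals. Keep the exercise-arm regression, labelled descriptive.

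**Sample size.** State that 80% power at 31 and 35 subjects is for an association within the exercise arm. Add the power of the group × marker test with its assumptions: about 79% (TLCO) and 74% (RVSP) with 58 per arm if the slope holds in all ILD, and about 59% and 53% within IPF.

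**Cost.** Wording only, since both arms already supply the data. The price is a less favourable stated power for the severity question, and the protocol's language about certainty and optimal timing should be softened to match.

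### The hypothesis is that severity governs response in IPF but not in other ILD, yet the response regression names no aetiology-by-severity term and, run as listed, cannot test it

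*Protocol article*

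**What the plan says.** **Hypothesis (Background).** For other ILD, "exercise training will be effective regardless of disease severity in patients with non-IPF related ILD". For IPF, "in patients with IPF, the response to exercise training will be greatest in those with less severe disease". The section bases this on an earlier uncontrolled study of 44 people with ILD of mixed aetiology, where milder disease went with larger gains in IPF. Of the remainder it reports: "This relationship was not seen in subjects with other ILDs".

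**Analysis (Statistical analysis).** One multiple regression, with change in 6MWD after exercise training as the outcome, is to show who responds best and when training should be offered. Its predictors are "Baseline demographic and physiological variables such as age; gender; disease aetiology; percent predicted TLC; percent predicted FVC; TLCO; pulmonary artery pressure" and desaturation on exercise. Subgroup analyses for IPF, dust-related and connective tissue disease-related ILD are announced just before this, directly after the comparison of exercise with control.

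**Power (Sample size).** For TLCO, the trial "with 80% power will require 31 subjects in the pulmonary rehabilitation group". The basis is given as: "This assumes that the true change in 6MWD is 15 meters for each 10% change in baseline percent predicted TLCO". For right ventricular systolic pressure (RVSP) the figures are 35 patients and 17 m per 10 mmHg. Both come from the same earlier study. The section does not say whether the slopes, or the 31 and 35 patients, refer to IPF or to all ILD.

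**The concern.** A severity effect that exists in IPF and is absent elsewhere is an interaction between aetiology and severity. In a regression where aetiology stands beside TLCO and pulmonary pressure as a separate predictor, aetiology shifts the mean change and each marker has one slope for everyone. That slope is a weighted average of the IPF and non-IPF slopes.

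If the hypothesis is true, a significant average slope would suggest that severity matters in all ILD, contrary to what is expected outside IPF. A non-significant one could hide a real effect in IPF. Neither result tests the hypothesis. The question of when to offer training, which is the trial's second aim, would be answered from a coefficient that describes neither group.

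**Working it through.** **Inputs from Sample size.** Exercise arm: 36 IPF + 11 dust-related + 11 connective tissue disease-related = 58, so 22 are non-IPF. Slopes: 15 m per 10% TLCO and 17 m per 10 mmHg RVSP. SD of change in IPF: 43 m. Stated requirements: 31 and 35 patients at 80% power.

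**Assumptions.** Two-sided 5% test; non-IPF slope of zero; one severity marker plus aetiology in the model; no losses. The SDs of TLCO and RVSP and the residual SD are not given.

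**1. The plan's own figures.** The subgroup sizes reproduce: the t-based two-sample calculation gives 36, 27, 11 and 11 per arm. The 31 and 35 cannot be reproduced without the missing SDs, so they serve as calibration. For the t test of a slope, write the non-centrality as √(n·f), where f is the explained-to-residual variance ratio. Solving for 80% power gives:

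- TLCO, n = 31: f = 0.271, r = √(f/(1+f)) = 0.46, implied SD of TLCO = 0.46 × 43/1.5 ≈ 13 points.
- RVSP, n = 35: f = 0.238, r = 0.44, implied SD of RVSP = 0.44 × 43/1.7 ≈ 11 mmHg.

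Fisher's z gives r of 0.485 and 0.458, and SDs of about 14 and 12.

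**2. The averaged slope.** With equal severity spread, the weight on the IPF slope is 36/58 = 0.62.

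- TLCO: 15 × 36/58 = 9.3 m per 10%. This is 38% below the IPF value (1 − 36/58) and 9.3 m above the non-IPF value.
- RVSP: 17 × 36/58 = 10.6 m per 10 mmHg.

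**3. Power if 15 m and 17 m are IPF slopes.**

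| Test | Non-centrality | TLCO | RVSP |
|---|---|---|---|
| Common slope, n = 58 | √(58f) × 36/58 = 2.46; 2.31 | 68% | 62% |
| IPF slope only, n = 36 | √(36f) = 3.12; 2.93 | 86% | 81% |
| IPF minus non-IPF slope | √(f/(1/36 + 1/22)) = 1.92; 1.80 | 47% | 42% |

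Simulation of the common-slope model (20,000 runs) gives about 64% for TLCO and 59% for RVSP. Calibrating by Fisher's z and using the subgroup SDs of 43, 40 and 30 m gives 70% and 65%. The common-slope range is therefore about 59–70%. Across methods the slope-difference test stays below 50%.

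**4. Unequal severity spread.** If the severity variance in non-IPF is v times that in IPF, the weight becomes 36/(36 + 22v). For v = 0.5 the average TLCO slope is 15 × 36/47 = 11.5 m and power is 77% (RVSP 71%). For v = 2 it is 15 × 36/80 = 6.75 m and power is 54% (RVSP 49%). A normal approximation puts these last two at 53% and 48%. The wider range is about 48–77%.

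**5. Power if 15 m and 17 m are all-ILD averages.** The non-centrality is √(58f) = 3.97 (TLCO) and 3.72 (RVSP), giving 97% and 95%. There is no shortfall. If the non-IPF slope were still zero, the IPF slope behind a 15 m average would be 15 × 58/36 = 24.2 m, and the common slope would still misdescribe both groups.

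**The case against.** The predictor list is introduced as examples, and nothing says main effects only. A journal article may leave model terms to a fuller document. A reader might infer that the plan commits to a single common slope; the text does not support that, because it omits an interaction without excluding one. This limits the wording of the point but does not remove it. The article gives the outcome, type of model, candidate predictors and power for this analysis, and states the hypothesis, and those parts do not fit together.

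The subgroup analyses might be meant to cover the regression too. Their position after the between-arm comparison makes their scope unclear at best, and treatment effects by aetiology do not estimate severity slopes. The randomisation blocks do split TLCO at 40% within IPF only. That shows severity within IPF was in mind, but it governs balance between arms, not the analysis.

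A reader might also infer that the trial misses its stated 80% power. That needs the 15 m and 17 m to be IPF slopes fitted in a pooled model. The Background makes an IPF origin plausible, but Sample size does not state it and the source study is not at hand. Nor should power be worked out for 31 or 35 patients of mixed aetiology: those are minimum requirements, no such analysis is planned, and the planned exercise arm is 58.

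Finally, benefit regardless of severity need not mean a slope of exactly zero outside IPF. This objection stands: the zero is a working assumption, and a smaller non-zero slope would shrink the distortion.

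**Conclusion.** The point holds as a mismatch between hypothesis and analysis. The hypothesis is a difference in severity slopes; the regression as listed names no term that estimates that difference, and nothing ties the subgroup analyses to it. On the working assumptions (IPF slope 15 m per 10% TLCO, zero elsewhere, 36 and 22 trained patients, equal spread) the single slope would be about 9.3 m and would describe neither group. This conclusion does not depend on how the power figures are read.

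A loss of power is conditional. With IPF slopes, the common-slope test has about 59–70%, or about 48–77% if severity spread differs between groups. With all-ILD slopes it has about 95–97%. An IPF-only slope in the planned 36 patients has about 81–86%, for a single marker and before losses. Overlap with other predictors would lower these figures: a variance inflation factor of 1.5, with the fuller model's degrees of freedom, would take the IPF-only values to about 69% and 63%.

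The primary between-arm comparison of 6MWD at nine weeks is not affected.

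**What to change.** **Statistical analysis.** In the response regression, fit separate TLCO and RVSP slopes for IPF and non-IPF (an IPF-by-TLCO and an IPF-by-RVSP term). Report the IPF slope, and the IPF minus non-IPF slope difference as the test of the Background hypothesis, each with a 95% CI. Say whether the aetiology subgroup analyses extend to this regression.

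**Sample size.** State which population the 15 m and 17 m slopes and the 31 and 35 patients describe. The sponsor should settle this from the source study; it should not be assumed that they are IPF figures. Give the SDs of TLCO and RVSP and the significance level, so that 31 and 35 can be checked. State the power of the slope-difference test, about 41–48% on the assumptions above.

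**Cost.** Wording and two extra coefficients, with no new patients or measurements. If the 31 and 35 are IPF requirements, the planned 36 IPF patients in the exercise arm already meet both before losses. The drawback is an imprecise slope difference, so a non-significant result must not be read as evidence that the slopes are equal.
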